## Abstract

**Introduction:**

One in eight women suffer from depression during pregnancy. Currently, low-intensity brief treatment based on cognitive behavioural therapy (CBT) is the only talking treatment widely available in the National Health Service (NHS) for mild and moderate depression. CBT involves identifying and changing unhelpful negative thoughts and behaviours to improve mood. Mothers in our patient advisory groups requested greater treatment choice. Interpersonal counselling (IPC) is a low-intensity version of interpersonal therapy. It may have important advantages during pregnancy over CBT because it targets relationship problems, changes in role and previous losses (eg, miscarriage). We aim to compare CBT and IPC for pregnant women with depression in a feasibility study.

**Methods and analysis:**

A two-arm non-blinded randomised feasibility study of 60 women will be conducted in two UK localities. Women with depression will be identified through midwife clinics and ultrasound scanning appointments and randomised to receive six sessions of IPC or CBT. In every other way, these women will receive usual care. Women thought to have severe depression will be referred for more intensive treatment. After 12 weeks, we will measure women’s mood, well-being, relationship satisfaction and use of healthcare. Women, their partners and staff providing treatments will be interviewed to understand whether IPC is an acceptable approach and whether changes should be introduced before applying to run a larger trial.

Several groups of patients with depression during pregnancy have contributed to our study design. A patient advisory group will meet and advise us during the study.

**Ethics and dissemination:**

Study results will inform the design of a larger multicentre randomised controlled trial (RCT). Our findings will be shared through public engagement events, papers and reports to organisations within the NHS. National Research Ethics Service Committee approved the study protocol.

**Trial registration number:**

ISRCTN11513120.

Strengths and limitations of this studyThis study uses a two-centre randomised controlled trial design to determine the feasibility of a definitive trial.Two methods of identifying participants will be used: through community midwives at booking and through ultrasound scanning clinics.Two talking therapies will be offered to assess the acceptability of these interventions during pregnancy.A process evaluation will explore the fidelity of intervention delivery and the experience of women, partners (or a significant other) and therapists.A definitive trial would be necessary to evaluate the effectiveness of the intervention.

## Introduction

Antenatal depression is common, with a reported prevalence of 11%^1^ and a point prevalence of up to 44% in certain populations.^2^ Antenatal depression is associated with a range of poor outcomes including continuing depression into the postnatal period, reduced breastfeeding rates,^3^ infant developmental delay^4^ and social/emotional problems, including depression in the offspring during adolescence.^5^ Pregnancy does not appear to be protective against developing depression or relapsing in those with a previous history of depression.^6^

Currently, the Whooley questions are used to identify women who may have antenatal depression.^7^ This screening method has high sensitivity (95%) and modest specificity (65%) for antenatal depression.^8^ However, anecdotal evidence suggests that women are not always aware that they are referred for further help following a positive Whooley screen.^9^

There is limited evidence for the effectiveness of psychological interventions for antenatal depression,^10^ despite a widespread reluctance of mothers to take antidepressants during pregnancy^11^ with 75% of women discontinuing antidepressant medication in the first trimester.^12^ There is also concern among clinicians about prescribing antidepressant medication,^13^ largely due to a lack of evidence regarding their safety,^14^ indicating that psychological interventions are particularly important at this time.^10 15^ One study found that women who discontinue antidepressant medication during pregnancy are five times more likely to experience a relapse in their depression requiring treatment.^6^ The current treatment recommendation for mild to moderate depression, including depression that occurs during pregnancy, is a brief, one-to-one supported self-help approach using the principles of cognitive behavioural therapy (CBT) known as low-intensity CBT.

### Theoretical basis of CBT and limitations for this population

The theoretical basis of CBT is that individuals prone to depression hold dysfunctional beliefs and therefore see the world through a negative filter.^16^ Adversity, such as pregnancy, triggers these underlying beliefs and prone individuals then behave in a way that is consistent with these negative beliefs thus triggering and reinforcing depression. There is no specific relevance of this model to pregnancy and it relies on the skill of the therapist to adapt CBT to individual circumstances. Although there is a growing evidence base for ‘high intensity’ CBT delivered by experienced therapists for perinatal depression, ‘low-intensity’ CBT is briefer and delivered by less experienced practitioners who have limited scope to adapt to the perinatal context and be flexible in its use. The use of high-intensity CBT is limited within current clinical frameworks due to limitations in funding and therapist availability. CBT has few explicit strategies to manage many of the problems that are common for women with antenatal depression, including role transitions and problems in relationships.

A recent review highlighted the need for more personalised therapies to treat perinatal depression, including interpersonal psychotherapy as a plausible treatment option.^17^ Women in our patient advisory group consultations reported that CBT is ‘too clinical’ and ‘inflexible’ with practitioners not appearing to consider the circumstances of pregnancy. This may be one reason why the uptake of CBT treatment for antenatal depression is low. It has been reported that 14% of women with antenatal depression receive psychological treatment and only 5% with antenatal depression achieve remission following treatment.^18^ Women who are pregnant receive lower rates of psychological intervention than those outside the perinatal period (30% vs 50%) despite an increased need for psychological treatment rather than drug treatment at this time.

### Theoretical basis of interpersonal counselling and advantages for treating antenatal depression

Interpersonal counselling (IPC) is a brief treatment which may be more appropriate for addressing the problems that depressed women have during pregnancy and postnatally. It is derived from interpersonal therapy, which holds that interpersonal relationships are a basic human need and attachment to key individuals provides a secure base from which to manage stressful events and conditions.^19^ Problems in interpersonal relationships can trigger symptoms of depression, such as low mood or sleeplessness, and these symptoms further compromise relationships leading to a downward spiral.^20^ This is particularly relevant to pregnancy as conflict in relationships and poor social support are the strongest risk factors for antenatal depression.^21^

IPC offers a more structured version of IPT that promotes understanding of depression through psychoeducation, problem solving and active involvement of the people in the person’s life to provide support and promote recovery. IPC helps individuals develop useful strategies to manage interpersonal conflict and can involve the partner if appropriate. It also focuses on approaches that help manage changes in role, conflict, isolation and loss (ie, miscarriage, stillbirth, termination, previous loss of would be grandparents) and the impact of these on relationships. By directly approaching these issues, IPC addresses what is theoretically central to depression and what service users report are significant worries and concerns for them. The approach is simple and focused and could be provided by practitioners who have limited training or experience.

Currently, there are limited data on the effectiveness of IPC.^14^ It is critical to test its effectiveness because although almost half (43%, n=2 01 591 in 2015–16) of all individuals who receive a talking treatment in the National Health Service (NHS) will receive a brief, ‘low-intensity’ treatment, interpersonal brief treatment approaches are currently not available in the NHS.^22^

IPC has been clearly developed and rigorously manualised as an intervention allowing assessment of fidelity to the model. Although there have been very few studies of the effectiveness of IPC, and none in the UK, one study of depression in primary care in Italy found IPC to be more effective than antidepressants Selective serotonin reuptake inhibitor (SSRIs) particularly for those with less severe depression,^23^ and a small UK pilot study found that IPC is an effective and acceptable treatment for young people with primarily depressive symptoms.^24^ A small feasibility study of IPC for antenatal depression in the USA among low-income mothers indicated high satisfaction with IPC and some improvement in mood.^25^

There are therefore good reasons to hypothesise that IPC may be more acceptable at this time and particularly effective in treating antenatal depression. There is some evidence that interpersonal therapy (IPT), a high-intensity therapy from which IPC is derived is more acceptable than 'high intensity' CBT, with sessions more likely to be attended and that outcomes are better for IPT than 'high intensity' CBT in existing psychological treatment services.^22^ We argue that evaluating this intervention for treating antenatal depression is particularly important because:

The model is particularly relevant to pregnanc,y and therefore the advantages of this approach over standard CBT treatment may be greater than at other times.^26^Psychological treatment provision is a priority at this time because of the potential risks of antidepressants during pregnancy and the costs of depression during pregnancy.^27^

Training low-intensity practitioners in IPC has the potential to offer women an acceptable, empirically valid option which may prove to be more effective than CBT and provide the NHS with a treatment option that may be both effective and cost-effective.

### Aims and objectives

Our overall aim is to improve psychological treatment for depression during pregnancy to improve outcomes for the mother, infant and the wider family. We aim to test whether six sessions of IPC are acceptable, effective and cost-effective for treating mild to moderate antenatal depression compared with the most commonly provided existing intervention, low-intensity CBT. Both interventions are one-to-one therapies comprising up to six sessions.

The aim of this first study is to establish the feasibility and acceptability of conducting a full-scale randomised controlled trial (RCT) to compare the effectiveness of these two low-intensity interventions for antenatal depression. Using a pragmatic study design operating within the existing care pathway, we will explore whether a full-scale trial using such a design is feasible. Study objectives are shown in Box 1.

Box 1:Detailed study objectivesTo determine whether a full trial is feasible by assessing:Whether staff who currently deliver low-intensity interventions within routine psychological treatment services, known nationally as Improving Access to Psychological Treatment (IAPT) services, can reliably deliver this newly adapted therapy after brief, additional training.Whether it is possible to recruit women from community midwife booking clinics and through screening at the ultrasound scanning clinics.Whether it is feasible and acceptable to randomise women following assessment.How acceptable IPC is to women, partners and those delivering the intervention relative to low-intensity CBT, assessed through qualitative interviews.Whether it is possible to collect sufficient outcome data, including those required to perform an economic evaluation.

## Methods and analysis

### Study design

This feasibility study over 21 months will be carried out in two centres (site A and site B) in preparation for a pragmatic fully powered RCT. Women with mild to moderate depression during pregnancy considered suitable for a low-intensity intervention will be randomised 1:1 either to the usual low-intensity treatment (CBT) or to a novel treatment called IPC.

### Study population, setting and recruitment plan

Women who are aged 18 years or over are eligible for inclusion between 10 and 24 weeks of pregnancy, with an Edinburgh Depression Scale (EPDS) score of 10 or above and mild or moderate depression according to Clinical Interview Schedule Revised (CIS-R),^28^ which gives an International Classification of Diseases 10th Revision diagnosis, whether or not they are taking an antidepressant. Both primiparous and multiparous women will be eligible. Recruitment will continue for 9 months.

We will exclude women with psychotic illness, organic brain disorder, bipolar disorder, personality disorder, alcohol or substance dependency, which will be identified through self-report. Also excluded will be those judged to be at high suicide risk in assessor’s judgement or from response to items on suicide in CIS-R or EPDS, those with severe depression according to CIS-R criteria and those who have had CBT or IPT within the last 6 months. If women miscarry or have a termination during the trial, they will be offered the opportunity to continue with the treatment but will not be included in the rest of the study.

We will compare recruitment through two routes which have been used successfully in two previous trials of antenatal depression and antenatal anxiety.^29 30^

Method 1: Women will be identified at community midwife booking clinics (around 8–10 weeks’ gestation) through the routine screening undertaken for depression using the Whooley questions.^8^ Those who answer ‘yes’ to either question and are considered by the midwife to be appropriate for further assessment for talking therapy, will be asked for their consent to be contacted by the research team about the study.

Method 2: Women will also be identified from ultrasound scan clinics where they will be given study information, eligibility screening questions (EPDS) and a form to indicate their willingness to be contacted by the research team for assessment if screening positive (EPDS 10 or above). This approach will provide a good opportunity to recruit disadvantaged groups, as attendance at scanning clinics does not appear to be socially patterned.^31^

Where needed, interpreters will be used to ensure that those who do not have English as a first language can be offered therapy.

Figure 1 shows the flow of participants through the trial.

**Figure 1 F1:**
[figure not shown]
ADAGIO study flow diagram. CBT, cognitivebehavioural therapy; CIS-R, Clinical Interview Schedule Revised; EPDS, Edinburgh Depression Scale; IAPT, Improving Access to Psychological Therapies; IPC, interpersonal counselling.

### Assessment and randomisation

A researcher will conduct a telephone assessment with women who consent to be contacted. At a subsequent face-to-face meeting, the researcher will establish eligibility for the trial, obtain written consent and collect baseline data. Partners will also be asked for their consent either in person at the baseline visit, online or by post.

Randomisation will be carried out remotely by Bristol Randomised Trials Collaboration randomisation service. It will be stratified by recruiting centre and minimised by parity (with random block sizes).

### Treatment arms

We have embedded the treatments within existing psychological treatment services available in primary care (Improving Access to Psychological Therapies (IAPT)). For women with mild or moderate depression during pregnancy considered suitable for a low-intensity intervention, we will compare up to six sessions of either low-intensity CBT or IPC.

### Data collection and management

All data collected and analysed during the study will be pseudoanonymised using a unique identifier. A record of trial participants’ names and contact details and assigned trial numbers will be maintained by the trial coordinator and stored separately and securely for administrative purposes. Study data collected by the research team will be recorded on study-specific data collection forms (CRFs). Data will then be entered onto a REDCap database.

### Baseline measurements

Baseline data will be collected at an initial face-to-face assessment with women and will include measures of mood, quality of life, quality of relationship with partner and antenatal attachment. Partners will also be invited to complete a depression rating scale.

### Follow-up measurements

Assessments will be completed either online by participants or over the telephone with a researcher 12 weeks following randomisation. This allows time for women to be allocated to therapy and to complete the sessions. Non-responders will receive two automatic online or telephone reminders 1 week apart, with attempts to collect data by telephone a week later if necessary.

### Measures at baseline and 12 weeks

CIS-R a computerised structured psychiatric interview (at baseline only).EPDS^32^ continuous and binary scores from women and their partners. The scale, sometimes known as the Edinburgh Depression Scale, was developed for postnatal depression but is widely used during pregnancy and has been validated outside the postnatal period and for men.^33 34^The Revised Dyadic Adjustment Scale^35^ assesses partner satisfaction.Maternal Antenatal Attachment Scale.^36^Health economic measures outlined below (EQ-5D-5L, ReQol10).At 12 weeks only: the number of sessions attended, number that include the partner, whether step up to more intense psychological intervention is needed, use of medication and use of secondary mental health services.

### Blinding

It will not be possible for assessors or participants to be blind to allocation; however, the statistician will be blind to allocation of participants.

### Outcomes

The primary outcome will be the proportion of eligible women successfully recruited to the point of randomisation.

We will assess numbers and proportions of participants:

Recruited for assessment (comparing two methods of recruitment).Randomised.Completing the course of treatment.Completing follow-up measures.Requiring ‘step up’ to a higher intensity intervention.

We will assess the acceptability of the recruitment method, intervention and study design through a series of in-depth interviews with participants and IAPT practitioners.

The primary outcome for a future trial is likely to be changed in EPDS score, but we will also consider the other secondary outcomes collected in this trial.

### Sample size determination

As this is a feasibility study, the sample size should be sufficient to measure feasibility parameters and data completeness with adequate precision.

There are around 3000 pregnancies per year at site A and 1500 at site B (total 4500) in the relevant IAPT catchment areas, giving a total of approximately 3375 pregnancies in the 9-month recruitment period. Assuming 10% of these have mild–moderate antenatal depression (338) and recruiting through both midwives booking appointments and ultrasound scanning clinics, we aim to include 60 women. This target of 60 subjects from 338 potentially eligible women (17.8%) gives a 95% CI for recruitment between 13.9% and 22.3%.

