### Data analyses

#### Quantitative data analysis

As this is a feasibility trial, no formal statistical testing will be carried out. Instead, the analysis will focus on reporting data that will be used for planning and for assessing the feasibility of the full trial.

A Consolidated Standards of Reporting Trials flow diagram will be produced. Proportions with 95% CIs calculated using the Exact Binomial Method will be produced for:

Participants consented.Participants who are randomised with completed baseline measures.Participants randomised to IPC who complete it.Participants randomised to low-intensity CBT who complete it.Randomised participants lost to follow-up.Randomised participants who require ‘step up’ to a higher intensity intervention.Randomised participants who have complete outcome data.

Baseline characteristics and demographic characteristics will be tabulated by treatment group (defined by intention to treat) and overall. Means or medians together with appropriate measures of dispersion will be reported for continuous measures and proportions for binary measures. The follow-up outcome data (namely the EPDS, Revised Dyadic Adjustment Scale, Maternal Antenatal Attachment Scale, number of sessions attended, number of sessions partner attended, medication use and secondary health service use) will be reported in the same way. Plots will be used to examine the distribution of continuous outcomes.

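### The only precision figure (60/338, 95% CI 13.9% to 22.3%) is a projection of reach on an assumed denominator, not the precision of the primary outcome

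*Protocol article*

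**What the plan says.** Under Sample size determination, the protocol article sets the aim that "the sample size should be sufficient to measure feasibility parameters and data completeness with adequate precision". It takes 3000 pregnancies a year at site A and 1500 at site B, "giving a total of approximately 3375 pregnancies in the 9-month recruitment period". The next step is "Assuming 10% of these have mild–moderate antenatal depression (338"), and from that pool "we aim to include 60 women". The section closes with its only interval: "This target of 60 subjects from 338 potentially eligible women (17.8%) gives a 95% CI for recruitment between 13.9% and 22.3".

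Under Outcomes: "The primary outcome will be the proportion of eligible women successfully recruited to the point of randomisation". The article does not define the denominator further.

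Under Study population, setting and recruitment plan, eligibility requires age 18 or over, 10 to 24 weeks of pregnancy, an EPDS of 10 or above, mild or moderate depression on the CIS-R, and none of several exclusions, among them high suicide risk and recent CBT or IPT. Women enter either through a positive Whooley screen, the midwife's view that they are suitable and consent to be contacted, or through a positive EPDS at a scan clinic and willingness to be contacted. Under Assessment and randomisation, a telephone assessment comes next and then: "At a subsequent face-to-face meeting, the researcher will establish eligibility for the trial, obtain written consent and collect baseline data".

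**The concern.** The sample size section and the primary outcome appear to describe the same proportion, but they rest on different populations. The 338 is a prevalence assumption multiplied by a projected number of pregnancies. A depressed woman who screens negative, is not put forward by her midwife or declines contact never has a CIS-R, so she is never classified as eligible or ineligible. Nothing in the described pathway turns 338 into an observed number. It is also not the number eligible, because only a depression rate has been applied.

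A reader who takes 13.9% to 22.3% as the precision of the primary result would expect about 4 points either way on a quantity near 18%. The proportion the study can observe is a different quantity, with a different expected value and a wider absolute interval. The study exists to plan a full trial, so a recruitment rate carried forward with the wrong denominator could mislead decisions on centres and duration.

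**Working it through.** **Inputs.** From the article: 3000 + 1500 = 4500 pregnancies a year; 9 months of recruitment; 10% assumed prevalence of mild to moderate depression; target 60; exact binomial 95% intervals (Quantitative data analysis); a reported antenatal depression prevalence of 11% (Introduction). Assumed, because the article gives no figure: 70 to 200 women confirmed eligible, and 80% follow-up as an illustration.

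**Formula.** For x out of n, the exact (Clopper-Pearson) limits are the 2.5% quantile of Beta(x, n − x + 1) and the 97.5% quantile of Beta(x + 1, n − x). Half-width is half the distance between the limits.

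**1. The plan's own figure.** 4500 × 9/12 = 3375; 3375 × 0.10 = 337.5.
- 60/338 = 17.8%, limits 13.83% to 22.25%.
- 60/337 = 17.8%, limits 13.87% to 22.31%, which round to the stated 13.9% and 22.3%.

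The stated interval is an exact binomial one, correct to within 0.1 point. Its half-width is (22.25 − 13.83)/2 = 4.2 points.

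**2. Dependence on the assumed prevalence.** At the article's 11%, 3375 × 0.11 = 371, and 60/371 = 16.2% (12.6 to 20.3). One point of prevalence moves the estimate by 1.6 points, and the stated interval contains nothing for this uncertainty. The 11% covers antenatal depression generally, so it shows sensitivity and is not a better value for mild to moderate depression.

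**3. Women randomised over women confirmed eligible (assumed 70 to 200).**

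| Confirmed eligible | 60/n | Exact 95% CI | Half-width (points) |
|---|---|---|---|
| 70 | 85.7% | 75.3 to 92.9 | 8.8 |
| 80 | 75.0% | 64.1 to 84.0 | 10.0 |
| 100 | 60.0% | 49.7 to 69.7 | 10.0 |
| 120 | 50.0% | 40.7 to 59.3 | 9.3 |
| 150 | 40.0% | 32.1 to 48.3 | 8.1 |
| 200 | 30.0% | 23.7 to 36.9 | 6.6 |

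Half-widths run from about 7 to 10 points.

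**4. Data completeness, which the sample size section names.** 48/60 = 80% has limits 67.7% to 89.2%, a half-width of (89.2 − 67.7)/2 = 10.8, about 11 points.

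**The case against.** The section is open about what it does: it marks the 10% as an assumption, calls the women potentially eligible and speaks of a target. Any planning calculation uses assumed inputs, and the text calls the interval one for recruitment without naming the primary outcome. That stands as far as it goes. But this is the only interval given in support of 60 women, the primary outcome is recruitment, and the interval treats the assumed denominator as known.

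Absolute half-widths are also being compared at very different proportions. Relative to the estimate, 60/338 gives about 4.2/17.8 = 24%, 60/200 about 6.6/30 = 22%, 60/120 about 9.3/50 = 19% and 60/70 about 8.8/85.7 = 10%. On that scale the observable denominators do no worse. This stands: the point is that the stated precision belongs to another quantity, not that 60 women are too few.

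Three stronger readings are tempting, and the documents do not support them.
- *The primary outcome cannot be computed.* It can: eligibility is established at the face-to-face visit, so women randomised over women confirmed eligible can be counted there.
- *The analysis leaves the primary outcome out.* The listed proportions, such as "Participants who are randomised with completed baseline measures", carry no stated denominator, and a CONSORT flow diagram is promised. Silence on the denominator does not show that eligible women are not meant.
- *Precision was never worked out for the other proportions.* The article condenses a full protocol that is not shown, and an analysis plan may exist, so such tables may be there.

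**Conclusion.** The concern holds in a limited form. The interval of 13.9% to 22.3% is correctly calculated for 60/338, but 338 is an assumed population before most eligibility limits, and no described procedure counts it. It is a projection of reach and should not stand as the precision of the primary outcome. On women confirmed eligible, the half-width is about 7 to 10 points against the stated 4 or so, and the expected proportion is 30% to 86% against 17.8%.

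This rests on two things. The range of 70 to 200 confirmed eligible is an assumption with no source in the article. That 338 is never observed is inferred from the recruitment and assessment sections; the flow figure and the full protocol are not shown. If the team did mean to divide by 338, the binomial interval would still omit the uncertainty in that number.

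The matter should be corrected but is not critical: no formal testing is planned, the article ties no progression threshold to this interval, and the target of 60 is unaffected.

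**What to change.** - **Outcomes.** Define the primary outcome as women randomised divided by women confirmed eligible at assessment. Report beside it women randomised divided by screen-positive women approached. Take both from the CONSORT flow counts, with exact 95% intervals.
- **Sample size determination, the 17.8%.** Relabel it as an assumed reach that depends on the 10% prevalence, for example 16.2% at the article's 11%. Drop 13.9% to 22.3% as the precision of recruitment.
- **Sample size determination, precision.** State it on observable denominators: about plus or minus 7 to 10 points for 60 randomised out of an assumed 70 to 200 confirmed eligible. Because the section claims adequate precision for data completeness, also give about plus or minus 11 points for 80% follow-up of 60.

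The cost is rewording in two sections and a less favourable stated absolute precision. No extra patients are needed.
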